### 2.6. Study Procedure

The study will be consisted of three periods:

Period 1: from 8:00 p.m. of the first study day to 8:00 a.m. of the second study day. Subjects will be asked to fast overnight for 12 h, without consuming foods or drinks. Before 8:00 p.m. of the first study day, subjects are instructed to having fluid intakes as before. Strenuous exercise will not allowed in the 24 h before the study. The subjects will be asked to sleep before 11:00 p.m. and are not allowed to urinate before they get up in the morning. Anyone who fails to meet the above requirements has to let the investigators know.

Period 2: from 8:00 a.m. of the second study day to 8:00 a.m. of the third study day. Subjects will be asked to have water restriction for 24 h. Meals containing ≤75% of water will be provided by the study. All foods will be weighted before and after the subjects eat, with the aim of assessing the intake of water from food of the subjects. Baseline measurements including height, weight, waist circumferences, body composition, blood pressure, blood glucose and blood samples will be obtained following standardized procedures. The first urine samples will be collected and tested. Subjects will have MRI scans for about 15–20 min. All subjects will have two medical earplugs and will not be allowed to sleep or move, just lying down for 15–20 min. Tests of mood, cognitive performances and subjective sensation will be performed by investigators. During Period 2, the urine samples will be collected and sent to the hospital laboratory immediately to measure the related indexes. They will also be asked to go to bed before 11:00 p.m. and are not allowed to urinate before they get up in the morning.

Period 3: from 8:00 a.m. of the third study day to 10:35 a.m. of the third study day. Subjects will have water supplementation. They will be asked to arrive at the lab at 8:00 a.m. Measurements including weight, body composition, blood pressure, blood glucose and blood samples will be obtained as before. The first morning urine and blood samples will also be collected and tested. MRI scans, cognitive performances, mood and subjective sensation of the subjects will be performed. At 8:30 a.m., subjects in WS group 1, WS group 2, WS group 3 will be asked to drink 200, 500, and 1000 mL of purified water, respectively. The subjects in NW group will drink no water or other fluids. All the water will be offered in opaque containers which should be drunk within 10 min. All the water will be kept in 30 °C~40 °C to reduce the gastrointestinal discomfort of the subjects. During the interval of 90 min, all subjects will be asked to undertake normal activities in the room adjacent to the testing room. After water supplementation for 90 min (at 10:15 a.m.), weight, body composition, blood pressure and blood glucose will be measured. Urine and blood samples will be collected, stored and tested. MRI scans, cognitive performances, mood and subjective sensation will be measured again. The study procedure is shown in Figure 2.

Subjects will be asked everyday if they have fever, diarrhea or other illness during the study. During the three periods of the study, all subjects will not be allowed to undertake strenuous activities. After water supplementation, the gastrointestinal distress questionnaire will be conducted among the subjects to evaluate the discomfort.

The schedule of enrolment, interventions, and assessments is shown in Table 2.

### 2.7. Anthropometric Measurements

Height (H), waist circumference (WC), blood pressure (BP) (systolic pressure: SP; diastolic pressure: DP) and blood glucose (BG) will be measured by trained investigators using professional instruments, respectively, as showed in our previous study [22] (HDM-300; Huaju, Zhejiang, China; MyoTape waistline measurer; HEM-7051; Omrom, Jiangsu, China; One Touch Ultra Easy; Johnson, Shenzhen, China). (BMI: weight (kg)/height squared (m)); Body surface area (m^2^): (male: weight (kg)×0.0021+height (cm)×0.0057+0.0882, female: weight (kg)×0.0127+height (cm)×0.0073−0.2106) [23]. Body composition (BC) will be measured by trained investigators using human body composition analyzer (Inbody 720, Biospace, Seoul, Korea).

### 2.8. Urine and Blood Biomarkers

Urine will be collected by the subjects using self-designed containers and sent to the laboratory and be tested immediately. All urine samples will be stored at +4 °C before measurements. Urine osmolality will be assessed with the freezing point method by osmotic pressure molar concentration meter (SMC 30C; Tianhe, Tianjin, China). Urine specific gravity (USG) and urine pH will be tested by automatic urinary sediment analyzer with uric dry-chemistry method (H-800; Dirui, Changchun, China). Urine color (UC) will be measured by investigators using chromatogram spectrophotometer (CM-5, Konica Minolta, Tokyo, Japan).

Urine and blood electrolyte concentrations (including sodium, potassium, chloride, calcium, magnesium, and phosphate) will be tested by automatic biochemical analyzer with the ion-selective electrode potentiometer method (AU 5800; Beckman, Brea, CA, USA). Blood urea nitrogen concentration (BUN) and creatinine concentration (Cre) will be measured by automatic biochemical analyzer (AU 5800; Beckman, Brea, CA, USA). Plasma copeptin concentration will be measured using enzyme-linked immunosorbent assay for antigen detection (CEA365Hu, Cloud-Clone, Wuhan, China).

### 2.9. Definition of Hydrated Status

The balance between water output and water input defines the hydration status. Dehydration occurs when the water input is insufficient to replace the free water output, which is defined as the urine osmolality is greater than 800 mOsm/kg [24]. Optimal hydration is defined as the 24-h urine osmolality ≤500 mOsm/kg, middle hydration is defined when 24-h urine osmolality is between 500 mOsm/kg and 800 mOsm/kg [25].

### 2.10. Visual Analogue Scales (VAS) for Subjective Sensation

Subjects will be instructed to place a pencil mark anywhere on the 10-cm-line designed to quantitatively measure the subjective sensation of satiety, hunger [26], sleepiness [27] and thirst [28]. The higher the score, the more hunger, thirsty, and sleepy the subjects are, as shown in our previous study [22].

### 2.11. Profile of Mood States (POMS)

The POMS is a widely used, brief, standard inventory of mood states, including seven subscales on a 5-point, 40 adjectives, which examines tension, depression, anger, vigor and confusion, etc. [29], as shown in our previous study [22].

### 2.12. Cognitive Performances (CP)

Six different cognitive tests are administrated using a “primary cognitive ability” software from the Institute of Psychology, Chinese Academy Sciences (Beijing, China), to investigate the cognitive performances of subjects.

### 2.13. Vocabulary Test

The vocabulary test will be used to assess verbal comprehension. Subjects will be asked to choose the most accurate explanation of a single word displayed on the screen from five options. The test has 36 words, and there is only one most accurate option, two accurate options and two wrong options. When subjects choose the most accurate, accurate and the wrong option, they will receive scores of 2, 1 and 0, respectively [30]. The higher scores they receive, the better ability of verbal comprehension they have.

### 2.14. Similarities Test

Similarities test will be used to assess the verbal comprehension. Subjects will be asked to find the similarities of the two words on the screen and to choose the most accurate explanation of the similarities from five options [30]. The test has 32 vocabularies, and there is only one most accurate option, two accurate options and two wrong options. When subjects choose the most accurate, accurate and the wrong option, they will obtain scores of 2, 1 and 0, respectively. The higher they scores they get, the better ability of verbal comprehension they have.

### 2.15. Symbol Search Test

Symbol search test will be used to measure processing speed during the three periods. There is a line in the middle of the screen with two symbols above the line, and five symbols below the line. Subjects will be asked to find the corresponding symbol between the symbols above and below the line as much as possible within the time (120 s). The higher the scores, the better the processing speed the subjects have [30].

### 2.16. Operation Span Test

Operation span test will be used to evaluate the ability of working memory during the three periods. It consists of mental arithmetic task and remembering the Chinese-zodiac-signs task. Subjects will be asked to do the mental arithmetic task and simultaneously, remember the Chinese-zodiac-signs after each mental arithmetic task, then, subjects will be asked to recall the order of the Chinese-zodiac-signs. Every mental arithmetic task has a time limitation. When the order of the Chinese-zodiac-signs is right, the subjects will obtain 1 mark. The scores of the test is consisted of two parts, only when the correct rate reaches 80% of the total, will the scores be considered as valid scores [31].

### 2.17. Paper Folding Test

Paper folding test will be performed to assess the visual-spatial ability during the three periods. Subjects will be asked to imagine that there is a square paper folded in some way in their mind, and use a pencil to punch a hole in the paper, then open the paper, to imagine how many holes are on the paper. Subjects will choose one from five options. The test has 12 sections, and the order of the test is from easy to difficult. The numbers of the right potions will be calculated as the scores of the subjects, where a higher score is the better [32].

### 2.18. Portrait Memory Test

Portrait memory test will evaluate the ability of episodic memory during the three periods. The test consists of six portraits [33]. The six portraits will be shown one by one on the screen, and the last name, the work and the hobby of each portrait will be shown at the same time. When the six portraits have been shown for once, then, the portrait will occur in a different order. The subjects will be asked to recall the last name, the work and the hobby of the portrait on the screen. Then, the six portraits will showed for the second time in a different order, where the subjects will be asked to recall the last name, the work and the hobby of the portrait on the screen for a second time. When subjects choose the right last name, the right work and hobby of the portrait, they will score 2, 1, and 1, respectively.

### 2.19. The Magnetic Resonance Imaging of Brain (MRI)

All procedures will be handled by experienced technicians. The subjects will be asked not to move or to sleep, and to just lie down on the scanner bed until all the sequences have finished.

MRI is commonly used in studies of neurodegenerative diseases. In order to detect whether the hydration statuses will affect the brain functions, structures and blood flow, three MRI sequences will be used in this study.

Oblique fMRI can measure the neural activity during hydration status. ASL can assess the resting regional cerebral blood flow, and examine observed changes in BOLD signal, which may be due to changes in blood flow. The Oblique fMRI, ASL and A× 3D BRAVO can evaluate the effects of hydration statuses on whole brain volume, ventricular volume, BOLD response and the thickness of the cortex.

Brain image data will be obtained on a 3.0-T system (Discovery MR750 3.0T, GE, Fairfield, CT, USA, 32-channel head-coil) with a T1-weighted sequence by technicians, in the Affiliated Hospital of Hebei University in Baoding, Hebei Province, China. The MRI scans will be made of three sequences: Oblique fMRI (functional magnetic resonance imaging), arterial spin labelling (ASL, non-contrast) and A× 3D BRAVO (axial brain volume).

### 2.20. The Parameters of the Three Sequences

A× 3D BRAVO

The parameters are: Flip angle = 12°, FOV = 25.6 cm, phase FOV = 1.0 cm, slice thickness = 1.0 mm.

3D ASL MRI (Non-contrast, arterial spin labelling)

ASL data will be collected at rest on the same scanner using a pseudo-continuous ASL tagging scheme with a 3D interleaved spiral FSE readout. The parameters are: FOV = 24 cm, slice thickness = 4.0 mm, slice = 36.

Oblique fMRI (functional magnetic resonance imaging)

Oblique fMRI parameters are: TR = 2000 ms, TE = 30 ms, flip angle = 90°, FOV = 24 cm, phase FOV = 1.0 cm, slice thickness = 4.0 mm, spacing = 0, slice = 38.

### 2.21. Temperature and Humidity of the Environment

The temperature and humidity both indoors and outdoors at the study site will be measured using a temperature hygrometer each day during the three periods (WSB-1-H2, Exasace, Zhengzhou, China).

### 2.22. Statistical Analyses

Statistical analyses will be conducted using SAS 9.2 (SAS Institute Inc., Cary, NC, USA). One-way ANOVA or Kruskal-Wallis *H* test measurements will be used to investigate the effect of hydration statuses on the changes in urine indexes, plasma indexes, mood, cognitive performances and MRI scans among the four groups. The MRI data will be analyzed by professional analyst using MATLAB (Mathworks Inc., Natick, MA, USA) and SIENA (FMRIB Software Library, Oxford, UK). Two-sided significance levels will be set at 0.05 (*p* < 0.05) with 95% confidence intervals (95% CI).

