## Abstract

*Background*: Dehydration may affect cognitive performances as water accounts for 75% of brain mass. The purpose of this study is to investigate the effects of dehydration and water supplementation on cognitive performances, and to explore the changes of brain structures and functions using MRI. *Methods and Analysis*: A double-blinded randomized controlled trial has been designed and will be implemented among 64 college students aged 18–23 years from Baoding, China. Subjects will be asked to restrict water for 36 h. The first morning urine will be collected and urine osmolality measured. The fasting blood samples will be collected and osmolality and copeptin will be measured. Three MRI sequences, including fMRI, ASL and 3D BRAVO will be taken to observe the changes of whole brain volume, ventricular volume, BOLD response and the cortex thickness. Cognitive performances and mood will be performed with software and questionnaires, respectively. Subjects in the water supplementation groups 1, 2, 3 will drink 200, 500 and 1000 mL of water, respectively, while subjects in the no water supplementation group will not drink any water. After 90 min, urine and blood samples, MRI scans, cognitive performances and mood will be performed. One-way ANOVA will be used to study the differences among groups. *Ethics and Dissemination*: The study protocol has been approved by the Peking University Institutional Review Committee. Ethical approval project identification code is IRB00001052-16071. Results will be published according to the CONSORT statement and will be reported in peer-reviewed journals.

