Referring to the effects of dehydration on cognitive performances, there was only one study conducted in China, which was designed and implemented by our team. It was a randomized controlled trial conducted among 68 college students. The results showed that water supplementation of 400 mL could improve the adverse effects of hypohydration on cognitive performances (unpublished). However, the study only investigated males. The level of dehydration conducted before was mild, however, and moderate dehydration was not investigated. Moreover, the changes of brain structures and functions in dehydration and water supplementation by MRI have not been explored yet. Hence, we designed a randomized controlled trial to investigate the effects of dehydration after 36 h of water restriction and rehydration after water supplementation on cognitive performances and the changes of brain structures and functions in different hydration status among male and females in free-living conditions.

We hypothesize that dehydration has adverse effects on cognitive performances and mood. Dehydration will induce the decrease of whole brain volume and the increase of ventricular volume, the BOLD and the cortex thickness. After water supplementation, the cognitive performances and mood will be improved. There will be an increase in the whole brain volume and decreases in ventricular volume, BOLD, and the cortex thickness. Moreover, there will be significant differences in the effects of dehydration on aspects of cognitive performances, mood, and the structures and functions of the brain between males and females in dehydration and water supplementation.

The purposes of this study are, first, to evaluate the effects of dehydration induced by 36 h water deprivation on cognitive performances and mood. Second, to explore whether cognitive performances and mood will be improved after water supplementation. Third, to compare the changes of whole brain volume, ventricular volume, BOLD response and the thickness of the cortex using MRI between dehydration and rehydration. Fourth, to compare the differences between males and females. Finally, to provide more suggestions for the associations between water intake and cognitive performances, may offer more scientific basis to revise the adequate water intake for young adults.

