### 2.2. Sample Size Calculation

In a related study, the letter cancellation scores of subjects in the water group before and after water supplementation were 23.34 and 28.81, respectively [21]. According to the SAS procedures (SAS Institute Inc., Cary, NC, USA), with the power set at 0.8 and α set at 0.05, in addition, a 10% drop-out rate will be taken into account, so a total of 64 subjects will be needed, including half males and half females.

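### The only inferential test stated compares changes among the four arms; it cannot answer the dehydration aim or the sex aim, and it is valid but less efficient than ANCOVA for the water aims

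*Protocol article*

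**What the plan says.** The Introduction lists several aims. The first is "first, to evaluate the effects of dehydration induced by 36 h water deprivation on cognitive performances and mood". The second and third concern improvement after water and the MRI changes between dehydration and rehydration. The next is "Fourth, to compare the differences between males and females". The Discussion also counts the sex comparison among the study's strengths, and section 2.2 fixes an equal split of men and women.

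Section 2.22 gives one inferential method for urine, plasma, mood, cognitive and MRI outcomes: a one-way ANOVA or Kruskal-Wallis test "on the changes in urine indexes, plasma indexes, mood, cognitive performances and MRI scans among the four groups". The Abstract agrees: "One-way ANOVA will be used to study the differences among groups". Section 2.22 has no within-subject test, time factor, sex factor or covariate, and it does not say which two assessments define a change.

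Under section 2.6 every subject has the same 12 h overnight fast and the same further 24 h of water restriction. The arms first differ at 8:30 a.m. on the third day, when they receive 0, 200, 500 or 1000 mL. Section 2.4 has the outcomes measured three times.

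**The concern.** The aims and the stated test do not match. Randomisation separates the arms only at the water step. The dehydration effect is therefore a before-after change shared by all arms, and a test of differences among arms cannot see it. A one-way layout on arm likewise cannot contain a sex effect or a sex-by-arm interaction. If nothing else is fixed in advance, the first aim has no suitable stated test and the sex analysis would have to be chosen after the data are seen.

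The water aims are the only randomised question, and the arms are small. There the stated test is valid, but it does not use the pre-water value as a covariate.

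**Working it through.** **The plan's own figure.** Section 2.2 gives a total of 64 from "the letter cancellation scores of subjects in the water group before and after water supplementation were 23.34 and 28.81, respectively" (28.81 − 23.34 = 5.47), "with the power set at 0.8 and α set at 0.05" and "a 10% drop-out rate will be taken into account". No SD is given and the test is not named, so 64 cannot be reproduced. It is compatible with 14 per arm: 14/0.9 = 15.6, rounded up to 16, and 16 × 4 = 64. The calculations below therefore assume equal arms, 14 analysed per arm (56 in all) and about 7 per sex per arm. They use the two-sided 0.05 level of section 2.22. Effects are in SD units of the score and are assumed, as is r, the correlation between assessments.

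**Dehydration aim.** Simulation of 20,000 trials, r = 0.6, on the change from assessment 1 to assessment 2:

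| True common change | Four-arm ANOVA rejects | Paired test rejects |
|---|---|---|
| 0 | 5.1% | 4.9% |
| −1 SD | 5.0% | about 100% |

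The ANOVA rejection rate does not move with the dehydration effect.

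**Sex aim.** With the sexes balanced within arms, a sex difference adds to within-arm variance and not to differences among arms. For a true 1 SD sex difference the four-arm ANOVA rejects 2.3% and a direct male-female test 95.7%. With dose effects of opposite sign in the two sexes (±1 SD at 1000 mL), the four-arm ANOVA rejects 1.5%.

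**Water aims, covariate.** With equal variances (set to 1) before and after water:
- change score: residual variance 2(1 − r)
- ANCOVA: residual variance 1 − r²
- ratio: (1 − r²)/[2(1 − r)] = (1 + r)/2

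The ratio is 0.75 at r = 0.5, 0.80 at 0.6, 0.85 at 0.7 and 0.90 at 0.8.

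**Water aims, power.** The omnibus noncentrality is λ = 14 × Σ(μᵢ − μ̄)²/v, where v is the residual variance. At r = 0.6, v = 0.80 for change and 0.64 for ANCOVA. With a linear effect reaching 0.8 SD, the arm means are 0, 0.16, 0.40 and 0.80 (mean 0.34) and the sum of squares is 0.3632. So λ = 14 × 0.3632/0.80 = 6.36 for change and 14 × 0.3632/0.64 = 7.95 for ANCOVA. The same method for other response shapes, each with a largest effect of 0.8 SD, gives:

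| Response (0, 200, 500, 1000 mL) | Change-score ANOVA | ANCOVA, 3 df | ANCOVA, volume trend |
|---|---|---|---|
| Linear (0, 0.16, 0.40, 0.80) | 51% | 61% | 79% |
| Plateau from 200 mL (0, 0.8, 0.8, 0.8) | 64% | 75% | 54% |
| Peak at 500 mL (0, 0.4, 0.8, 0.4) | 46% | 55% | 23% |

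The 3-df ANCOVA beats the change-score ANOVA in every row. The trend test gains only when the response follows the dose. The covariate's advantage shrinks as r rises: for a linear effect of 1 SD, 61% against 75% at r = 0.5, and 96% against 98% at r = 0.8.

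**The case against.** The strongest reply is that this is a condensed article. Section 2.22 is a few sentences long, the Abstract assigns ANOVA only to differences among groups, and neither says that ANOVA will be used for the dehydration or sex aims or that no other test will be run. Paired tests and sex terms could sit in a fuller document. Part of this stands: a reader might infer that the authors intend to judge dehydration by a test that rejects 5% of the time whatever happens, and the text does not say so. But section 2.22 is not silent on method. It names a specific test, applies it to every outcome class, and that test cannot serve two of the stated aims.

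A reader might also infer that the plan ignores the pre-water value. The wording does not support that, because it analyses changes. If those run from before to after water, the value is subtracted, and the analysis is valid under randomisation. ANCOVA is a gain in efficiency, not a correction of bias.

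Finally, the ordered volumes might suggest that a trend test should come first. The protocol states no dose-trend hypothesis, and with an early plateau or a peak the trend does worse than even the stated test (54% against 64%; 23% against 46%).

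**Conclusion.** The mismatch holds. The only inferential test stated carries no information on the dehydration effect and cannot address the male-female comparison. Both follow from the design and the form of the test, not from any assumed effect size. For the water aims the finding is milder: a valid analysis that leaves 10% to 25% of residual variance unremoved for r between 0.8 and 0.5, or about 10 points of power in the cases worked at r = 0.6. These sizes rest on equal arms, 14 analysed per arm, normal outcomes and an assumed r.

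It does not follow that the trial cannot address the dehydration and sex aims. The three assessments supply the data, with limits: no arm stays hydrated, and the sex-by-arm cells are small.

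**What to change.** Amend section 2.22 to state an analysis for each aim.

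- **Dehydration:** a within-subject estimate of assessment 2 minus assessment 1, with 95% CI, over all subjects who have both. State that no arm stays hydrated, so practice effects from repeated testing are mixed with dehydration. State too that assessment 1 already follows the overnight fast.
- **Water:** ANCOVA of the post-water value on arm, pre-water (assessment 2) value and sex, with the 3-df arm test as the main test. A volume trend may be prespecified as a supplement, not a replacement.
- **Sex:** a male-female comparison of the assessment 2 minus 1 change, and a sex-by-arm term in the ANCOVA. Report both as estimates with CIs, and note that the sex-by-arm estimates are imprecise at about 7 per cell (equal allocation, 10% drop-out).

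A repeated-measures model with a free arm-by-time interaction is not a substitute for the ANCOVA. With complete pre- and post-water data it returns the change-score estimates and standard errors.

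The cost is wording, plus a degree of freedom each for the covariate and sex. No new data or visits are needed.

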**Figure 2 ijerph-15-01477-f002:**
[figure not shown]
The study procedure (Note: H (Height); W (Weight); WC (Waist circumference); BP (Blood pressure); BG (Blood glucose); BC (Body composition); CP (Cognitive performances); POMS (Profile of Mood States); VAS (Visual Analogue Scales); MRI (Magnetic resonance imaging)).

**Table 1 ijerph-15-01477-t001:** All items from the World Health Organization Trial Registration Data Set (SPIRIT checklist, item 2b).

Data Category	Information
Registration number	ChiCTR-IOR-17011568 Chinese clinical trial registry
Registration State	1008001 Prospective registration
Public title	The effect of hydration and water supplementation on the cognitive performance of college students
Scientific title	Effect of Different Hydration State on Cognitive Performance
Approval of ethic committee	Peking University Institutional Review Committee
Ethical approval project identification code	IRB00001052-16071
Date of approved by ethic committee	5 December 2017
Study type	Interventional study
Study design	Randomized controlled trial
Key inclusion and exclusion criteria	Inclusion criteria: Aged between 18 and 23; Male and Female; In health state, without metabolic disease, oral diseases, and so on. Exclusion criteria: Aged < 18, or age > 23; With metabolic disease, oral diseases, and other diseases.
Interventions	Water supplementation
Outcomes	Urine osmolality, Blood pressure, Mood, Thirsty, Cognitive performances, MRI scans
Collecting samples	Urine, Blood
Recruitment state	Started
Randomization Procedure (please state who generates the random number sequence and by what method)	Primary sponsor generates random sequence with random number table

**Table 2 ijerph-15-01477-t002:** The schedule of enrolment, interventions, and assessments.

Timepoint	Enrolment	Allocation	Post-Allocation	Close-Out
	5 April 2018	10 April 2018	15 April 2018	30 May 2018
Enrollment:				
Eligibility screen	X			
Informed consent	X			
Allocation		X		
Interventions:				
Water supplementation			X	
Assessments:				
Baseline anthropometric measurements variables: height, weight, waist circumference, blood pressure, blood glucose, body composition	X		X	
Outcome variables: cognitive performances, mood, subjective sensation, MRI			X	X

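### The aim that water improves cognition and mood has 13 co-equal outcomes, each tested at 0.05 by a four-group omnibus test, with no primary outcome, change interval or water-versus-no-water contrast named

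*Protocol article*

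**What the plan says.** Section 2.22 names the test: "One-way ANOVA or Kruskal-Wallis *H* test measurements will be used to investigate the effect of hydration statuses". It applies this to "changes in urine indexes, plasma indexes, mood, cognitive performances and MRI scans among the four groups", and sets the level once for all of them: "Two-sided significance levels will be set at 0.05". Confidence intervals at 95% are also planned there.

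Two of these domains are batteries. Section 2.12 states "Six different cognitive tests are administrated", and sections 2.13 to 2.18 describe them: vocabulary, similarities, symbol search, operation span, paper folding and portrait memory. Section 2.11 describes the mood inventory as "including seven subscales on a 5-point, 40 adjectives".

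The outcomes row of Table 1 reads "Urine osmolality, Blood pressure, Mood, Thirsty, Cognitive performances, MRI scans", with no ranking. The purposes at the end of section 1 do not rank outcomes either. Section 2.4 schedules three assessments, and section 2.22 does not say which two define the tested change.

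Section 2.2 sizes the trial on letter cancellation scores of 23.34 and 28.81, before and after water in the water group of a related study.

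**The concern.** The second purpose in section 1 is directional: whether cognition and mood get better after water. To answer it at a known error rate, the plan needs an outcome, a time interval and a comparison fixed in advance. It fixes none of these for this aim. It states a four-group omnibus test for each outcome, and a significant omnibus result does not say which arms differ or in which direction.

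The sample-size outcome often shows which endpoint is primary. Here it cannot, because letter cancellation is not administered.

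If a report rests the improvement claim on whichever of the 13 outcomes reaches significance, the stated 5% does not describe the error rate of that claim. Section 5 says the results may contribute to revising water intake values, so the difference is not trivial.

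**Working it through.** **Inputs**
- Level: 0.05 two-sided for each test (section 2.22).
- Test: omnibus comparison of four arms (section 2.22).
- Outcomes behind the aim: 6 cognitive tests (section 2.12) + 7 mood subscales (section 2.11) = 13.
- Subjects: 64 in total (section 2.2). The allocation ratio is not stated, so I assume equal arms: 64/4 = 16 each.
- Correlation between outcomes: not in the document. I assume a common value and show 0 to 0.7.

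**The plan's own figure.** A single pre-named outcome tested once has a false-positive rate of 5%, as stated. The total of 64 cannot be reproduced because section 2.2 gives no standard deviation. For this point it matters only that the difference used, 28.81 − 23.34 = 5.47, is a before-after change on a test outside the six.

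**Independent outcomes.** Chance of at least one rejection = 1 − 0.95^m.
- m = 6: 1 − 0.95^6 = 0.265
- m = 13: 1 − 0.95^13 = 0.487

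**Correlated outcomes.** I simulated null trials of 4 × 16 subjects with normal outcomes and one ANOVA per outcome.

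**Direction.** Under the null, half of the rejections favour water by symmetry, taking improvement to mean that the pooled water mean is better than the no-water mean. The rate per test is then 0.025. For independent outcomes:
- 1 − 0.975^6 = 0.141
- 1 − 0.975^13 = 0.280

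| Assumed correlation | 6 tests, any rejection | 13 outcomes, any rejection | 6 tests, favouring water | 13 outcomes, favouring water |
|---|---|---|---|---|
| 0 | 26% | 49% | 14% | 28% |
| 0.5 | 21–22% | 35% | 11% | 19% |
| 0.7 | 17% | 26% | 9% | 14% |

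The comparator is 5% for the any-rejection columns. For the favouring-water columns the like-for-like figure for one test is 2.5%. Those columns also exceed 5% throughout.

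**After the fix.** One outcome with one contrast at 0.05 gives 5%. If the outcomes stayed co-equal, Bonferroni would need 0.05/6 = 0.0083 for the six tests or 0.05/13 = 0.0038 for all 13.

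**The case against.** The best reply is that this is a condensed article and that a multiplicity procedure commonly sits in an analysis plan, which is not shown. That stands for Holm, Bonferroni and post-hoc methods: their absence is not the finding. It does not cover the primary outcome, which belongs in the protocol and registration. This article lists its outcomes and sets its level, but without a hierarchy.

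Some stronger readings are tempting, and the document does not support them.
- **Any single p < 0.05 proves improvement.** A reader might infer this rule, but no section states it. The aim is worded as exploring, and the remark on intake values is hedged.
- **The error is 58% or 66%.** Those figures need 17 or 21 outcomes, reached by adding the four visual analogue scales and then the four MRI measures. Section 2.22 does not assign the scales to a test, and an MRI result is not a cognition or mood result. Urine and plasma osmolality are there to confirm hydration status (section 4).
- **There is no comparison at all, or pairwise tests are planned.** A four-group omnibus test is stated. No pairwise tests are.
- **Every false positive would be read as benefit.** Only about half favour water, which is why the directional figures are given.

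The letter-cancellation mismatch is a sample-size matter in its own right. Here it shows only that no primary outcome can be read from section 2.2.

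**Conclusion.** The concern holds in this form: for the cognition-and-mood aim the protocol names no primary outcome, no change interval and no contrast with no water, and it tests all 13 outcomes at 0.05.

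With no true effect, the chance of at least one significant omnibus result is 17–26% for the six cognitive tests and 26–49% for all 13. Restricted to results favouring pooled water, it is about 9–14% and 14–28%.

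These ranges assume equal arms, normal outcomes, one omnibus test per outcome and a common correlation between 0 and 0.7. The correlation is an assumption and has the largest influence, but no value in that range brings the rate down to 5%. The figures describe what happens if any one of the outcomes can carry the claim. The document does not say that it will be used that way, but nothing in it prevents this.

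**What to change.** Before unblinding, state in the protocol and the registry:
1. **Primary outcome:** one of the six administered cognitive tests, chosen by the sponsor.
2. **Change:** from the dehydrated assessment on the third study day to the assessment 90 min after water.
3. **Contrast:** one comparison with no water, for example the pooled water groups against the no-water group, at two-sided 0.05.
4. **Secondary family:** the other five cognitive tests with Holm (smallest p-value against 0.05/5 = 0.01). If joint control over all six is wanted, test these only after the primary is significant; otherwise the two families together can reach 0.05 + 0.05 = 0.10.
5. **Exploratory:** mood, MRI, visual analogue scales, biomarkers and sex comparisons, reported as estimates with the 95% confidence intervals already planned.

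The cost is analysis wording and a registry update, with no new data. Fewer nominally significant results can be claimed, and a mood effect could no longer carry the main conclusion.
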